### 2.9. Blinding Procedure

To protect the blinding, patients will be informed that they will be assigned to one of two groups for an educational therapeutic treatment, without further details about the differences between the groups. A brief overview of both the TNE and the control content will be provided to patients without indicating which group they belong to. Patients will be told that the focus of the sessions will vary depending on the group they are in. Additionally, the lessons will be conducted in small groups, with patients from different arms scheduled on separate days and times, both in-person and remotely, to ensure that patients in one group only interact with others from the same group.

While the TNE expert will not be blinded to the intervention, the evaluation team (including the neurologist, QST expert, and neurophysiologist) as well as the data analyst will remain blinded to the patients’ group assignments to uphold the double-blind design. After the final (tenth) lesson, each patient will be asked to guess which group they believe they were assigned to in order to assess the effectiveness of the blinding process.

### 2.10. Plans for Analysis

An a priori calculation of the sample size was performed based on the primary endpoint. In line with studies on CM with MOH, we aim for a between group difference of 3.0 monthly headache days at T4 and a standard deviation of 4.5 [55]. Using an alpha error of 5%, a power of 80%, and a medium effect size, the calculated sample size is 70 patients. Considering a reasonable dropout rate, we plan to recruit 80 patients.

To assess the treatment’s effects on clinical and instrumental outcomes, a generalized linear mixed model for repeated measures (*p*-value < 0.05) will be performed on the primary outcome and, in a sub-analysis, on secondary outcomes. The model will include group and time as fixed effects, time by group as an interaction term, and the outcome as the dependent variable. Covariates will be selected from those identified as significantly different between groups [10]. A correlation analysis will also be conducted between migraine disability indexes and clinical/neurophysiological measures to identify potential biomarkers. False discovery rate correction will be applied to reduce type-I errors.

The number of adverse events (AEs) during the treatment period will be counted separately for the TNE-A and CON-A groups and classified according to common terminology criteria for adverse events (CTCAEs). An AE is defined as any adverse medical event associated with the use of a treatment in humans, regardless of whether it is considered related to the treatment. Causality (relationship to study treatment), action taken, and outcome will be summarized separately.

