## Abstract

Chronic migraine (CM) is a highly disabling condition, affecting about 2% of the global population. Non-pharmacological treatments can be optimal for their non-invasive nature. This prospective, randomized, double-blind, controlled trial aimed to test the efficacy of therapeutic neuroscience education (TNE) in CM. Early response biomarkers were also evaluated. A total of 80 CM patients were consecutively enrolled and randomly allocated to TNE or a general education program. Treatment effectiveness was evaluated at baseline (T1) and 2 months after the end of treatment (T4). We collected the responses to disability and comorbidity questionnaires at the start (T1) and end of treatment (T3, 10 weeks after start). Early response biomarkers were evaluated at screening (T0) and mid-way through the process (T2, 5 weeks after start). We expected that TNE would provide a greater benefit than the general education program, which served as the primary outcome of this study. We also expected that a change in clinical and neurophysiological measures could potentially occur, reflecting plasticity-induced reorganization and predicting clinical response. This is the first study selectively exploring the effect of TNE as a standalone treatment for CM. A new, effective treatment regime without interactions with other medication could be of great interest as an addition to migraine therapeutic strategies.

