The primary objective of this study is to evaluate the efficacy of TNE as a preventive treatment for CM compared to a general education protocol, with a focus on reducing monthly headache days from baseline to follow-up. Additionally, we aim to identify potential predictive factors through neurophysiological assessments.

The primary outcome is the reduction in migraine days, as the observed improvement should be at least comparable to that achieved with other therapies. Accurately predicting TNE effectiveness at baseline or early in the treatment process will help identify patients with a high likelihood of response, ensuring they receive appropriate long-term, high-commitment care.

We hypothesize that TNE will reduce monthly headache days and that mid-treatment changes in IDAP, nBR, and QST assessments will precede clinical improvement, serving as potential biomarkers.

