### 2.4. Study Design

After screening for inclusion/exclusion criteria (T0), patients will complete a headache diary for one month before entering the study (T1). At this point, they will undergo QST, neurophysiological assessments, and questionnaire evaluations before being randomly assigned to either the experimental (TNE-A) or control (CON-A) group (further details provided in the next section).

Following the 5th lecture (T2), patients will repeat the QST and neurophysiological assessment (T2). Headache frequency and questionnaire data will be collected again at the end of the 10-session program (T3). Additionally, headache burden will be reassessed two months after completing the TNE program (T4) (see Figure 1). This protocol follows the Standard Protocol Items: Recommendations for Interventional Trials (SPIRIT) guidelines [39] and is designed and will be reported in accordance with the Consolidated Standards of Reporting Trials (CONSORT) [40].

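### The trial is sized for an arm difference at T4, but the analysis text names neither the visits in the model nor the deciding contrast; an overall interaction over T1, T3 and T4 would not match the sizing

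*Protocol article*

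**What the plan says.** All references are to the protocol article.

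- **Sizing (section 2.10).** "we aim for a between group difference of 3.0 monthly headache days at T4", with an SD of 4.5. Then: "Using an alpha error of 5%, a power of 80%, and a medium effect size, the calculated sample size is 70 patients". With an unspecified dropout allowance this becomes 80: "Considering a reasonable dropout rate, we plan to recruit 80 patients".
- **Primary outcome (section 2.2).** The fall in monthly headache days between baseline and follow-up. Follow-up is not tied to a visit label there.
- **Time frame (Abstract).** "Treatment effectiveness was evaluated at baseline (T1) and 2 months after the end of treatment (T4"). The Abstract places the questionnaires at T1 and T3.
- **Data collection (section 2.4).** A one-month diary leads up to T1. Then: "Headache frequency and questionnaire data will be collected again at the end of the 10-session program (T3"). Headache burden is assessed once more at T4, two months after the programme.
- **Analysis (section 2.10).** The primary outcome goes into "a generalized linear mixed model for repeated measures" with fixed effects for group and time and their interaction, at p < 0.05. The same model is to be used for the secondary outcomes in a sub-analysis. No visit list, deciding term or contrast is given.

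**The concern.** The sizing fixes a single comparison, the arm difference at T4. The analysis fixes a set of model terms and a significance level, and nothing links the two. Because headache frequency exists at T1, T3 and T4, the natural way to fit a repeated-measures model is with a three-level time factor. Its group-by-time term is then a joint test, on 2 degrees of freedom, of any arm difference in change at T3 or at T4.

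Two things are at stake. A significant joint test could be reported as proof of benefit two months after the programme when the effect was present only at its end. And the stated 80% power belongs to a one-visit comparison, so it need not hold for the joint test.

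A smaller point follows from using one model for all outcomes. Responder status is defined as a reduction of more than 50% at follow-up, so nobody can be a responder at T1. A group-by-time term that includes T1 could not be estimated for it.

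**Working it through.** **Inputs from section 2.10:** difference 3.0 days at T4, SD 4.5, alpha 5%, power 80%, 70 patients (35 per arm; allocation is 1:1 in section 2.3).

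**Assumptions, not in the document:** two-sided alpha; SD σ = 4.5 at every visit; the same correlation ρ between any two visits, taken as 0.3, 0.5 and 0.7; complete data on 35 per arm.

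**Step 1. The plan's own figure.** n per arm = 2(1.96 + 0.84)² × 4.5² / 3.0² ≈ 35.3, so 70.6 in total, or 72 when each arm is rounded up. The stated 70 is reproduced within rounding. A one-sided calculation would give 56, so two-sided is the plausible reading. This is a two-group comparison at one time point.

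**Step 2. Formulas.** Let a and b be the arm differences at T3 and T4, with none at T1, and n = 35 per arm. The non-centralities are:

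- 2-df interaction over T1, T3, T4: λ = n(a² − ab + b²) / [3σ²(1 − ρ)]
- 1-df contrast of change from T1 to T4: λ = nb² / [4σ²(1 − ρ)]
- 1-df T4 difference with T1 as covariate: λ = nb² / [2σ²(1 − ρ²)]

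Example at ρ = 0.5, with σ² = 20.25:

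- a = 3, b = 0: interaction λ = 35 × 9 / 30.375 = 10.37; T4 contrast λ = 0.
- a = 1.5, b = 3: interaction λ = 35 × 6.75 / 30.375 = 7.78; change contrast λ = 35 × 9 / 40.5 = 7.78; covariate-adjusted λ = 35 × 9 / 30.375 = 10.37.

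Under linear build-up the interaction and the change contrast have the same non-centrality, so the second degree of freedom is pure cost.

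**Step 3. Probability of significance** (non-central F), at ρ = 0.3 / 0.5 / 0.7:

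| Arm difference at T3, T4 | 2-df interaction | Change T1 to T4 | T4 adjusted for T1 |
|---|---|---|---|
| 3, 0 (gone by T4) | 66 / 81 / 96% | 5% | 5% |
| 1.5, 3 (linear build-up) | 53 / 68 / 89% | 64 / 78.5 / 94% | 82 / 89 / 97% |
| 3, 3 (sustained) | 66 / 81 / 96% | 64 / 78.5 / 94% | 82 / 89 / 97% |
| 0, 3 (late only) | 66 / 81 / 96% | 64 / 78.5 / 94% | 82 / 89 / 97% |

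The loss under linear build-up is about 11, 10 and 5 points at the three correlations.

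**Step 4. Sensitivity.** With unequal correlations (T1–T3 0.5, T3–T4 0.7, T1–T4 0.4), the T3-only effect gives 96% for the interaction against 5%. Linear build-up gives 63% against 71% for the change contrast. With 40 per arm and ρ = 0.5, linear build-up gives 75% against 84%. For 80% power under linear build-up at ρ = 0.5, the interaction needs 90 patients in total, the change contrast 74 and the covariate-adjusted contrast 56.

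**Step 5. Two visits only.** If time has just the levels T1 and T4, the interaction has 1 df and is the change contrast. The first column of the table then does not apply. What remains is the gap between the last two columns: the variance of the change contrast exceeds that of the covariate-adjusted one by the factor 2/(1 + ρ), which is 1.54, 1.33 and 1.18 at the three correlations.

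**The case against.** The strongest reply is that a reader might infer that the plan makes the three-visit interaction its primary test, and the article does not say so. It lists model terms only. The Abstract ties effectiveness to T1 and T4 and leaves T3 to the questionnaires, and section 2.10 says the sizing is based on the primary endpoint and names T4. On that two-visit reading the mismatch disappears. An analysis plan that is not shown may also name the contrast. This stands, and it is why the point is conditional. It does not remove the point: the article does fix a model and a significance level for the primary outcome, collects headache frequency at T3, and contains nothing that keeps T3 out of that model.

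It is also fair to say that the size depends on correlations the document does not give, that an effect of 3 days at T3 and exactly zero at T4 is an extreme pattern, and that the joint test is slightly stronger than the change contrast for sustained or late effects. All of that stands.

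Two further inferences should be resisted. One is that MOH status, like responder status, cannot vary at T1. Section 2.1 admits patients with and without MOH, so it does vary. The other is that "The primary outcome is the reduction in migraine days" in section 1 sets up a different primary outcome. The same section, and sections 2.2 and 2.10, speak of headache days, so this is an editorial slip.

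Finally, keeping T1 as a repeated outcome is a legitimate method. Using it as a covariate gains efficiency; it does not correct an error.

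**Conclusion.** The point holds conditionally. The sizing is for T4, and the analysis text does not tie the primary test to T4. If the overall interaction over T1, T3 and T4 decides, the trial could be declared positive in about 66% to 96% of cases with a 3-day effect at T3 and none at T4. It would also have about 5 to 11 points less power than the T4 change contrast under linear build-up. There is no power loss for sustained or purely late effects, and no mismatch at all if only T1 and T4 enter.

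These figures rest on an SD of 4.5 at each visit, 35 completers per arm and assumed correlations of 0.3 to 0.7. On either reading, adjusting T4 for T1 headache days is more powerful than analysing change: 82%, 89% and 97% against 64%, 78.5% and 94%. The documents do not support the stronger statement that the planned test is the wrong one, because they do not say which test is planned.

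**What to change.** Amend section 2.10 before unblinding:

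1. State that the single primary test is the model-based between-arm difference in monthly headache days at T4, two-sided 5%. Take it from a repeated-measures model with T3 and T4 as outcomes and T1 headache days as a covariate, whose effect may differ by visit.
2. Label the T3 contrast and the overall interaction as secondary.
3. Analyse responder status as a between-arm comparison of proportions at T4, by risk difference or logistic regression, and not through a time-by-group term that includes T1.
4. As an editorial correction, use monthly headache days for the primary outcome in section 1.

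The cost is a few sentences. All the data are already to be collected, and no patients are added. If a separate analysis plan already names the T4 contrast, one sentence in section 2.10 that says so is enough for the first two items.

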## 2. Materials and Methods

### 2.1. Study Cohort

Consecutive CM patients will be recruited for the study. Eligibility criteria will include a CM diagnosis (with or without MOH) based on the International Classification of Headache Disorders (ICHD-3) criteria [32] and age > 18 years, as recent data suggest TNE is effective in older adults as well [33]. Patients will be enrolled consecutively. Exclusion criteria will include an ICHD-3 diagnosis of another primary or secondary headache disorder (except for MOH), neurological or psychiatric conditions that could affect compliance or neurophysiological assessments (e.g., neurodegenerative disorders, multiple sclerosis, epilepsy, schizophrenia, severe anxiety/depression with HADS >15), chronic pain conditions (e.g., low-back pain, chronic pelvic pain), severe comorbidities related to migraine or systemic diseases requiring concurrent medical treatment, and malignancy. Patients on migraine preventive therapy will be included if their prophylaxis has remained unchanged and ineffective for at least three months prior to recruitment. This treatment will not be down-tapered or discontinued at the study’s onset. Relevant demographic data will also be collected.

Migraine burden will be assessed throughout the study using a headache diary (tracking headache days, pain intensity, and acute medication use) and several validated questionnaires, including the Migraine Disability Assessment (MIDAS), the Headache Impact Test (HIT-6), the Central Sensitization Inventory (CSI), the Pain Catastrophizing Scale (PCS), and the Hospital Anxiety and Depression Scale (HADS) [34,35,36,37,38].

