### 2.2. Outcome Measures

The primary aim of the present study is to test the efficacy of TNE as a preventive treatment for CM compared to a general education protocol. The primary outcome will be the reduction in monthly headache days from baseline to follow-up. Secondary endpoints will include (i) the interruption rate of MOH; (ii) the proportion of patients achieving a >50% reduction in headache days (i.e., responders) at follow-up; (iii) differences in biomarkers (IDAP, nBR, and the QST) between responders and non-responders, along with the correlation between these biomarker values and clinical improvement in headache day reduction to assess their potential as efficacy predictors; and (iv) significant reductions in disability and migraine burden scores.

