### 2.3. Randomization, Schedule, and Adherence

Patients will be randomly assigned at a 1:1 ratio using a pre-generated randomization list created in SPSS by an experimenter who will not be involved in patient recruitment, treatment, or data analysis. Participants will be required to attend a full course of 10 lessons, with the first and last sessions conducted in person and the remaining eight delivered remotely via PowerPoint presentations. Lessons will be held in small groups, with the real and control education groups scheduled on different days to prevent interaction between participants from different study arms. The treatment will be considered valid if patients attend at least 8 out of 10 lessons. In case of absence, the PowerPoint presentation from the missed session will be sent to the participant. Additionally, a brief Q&A session will be conducted before the next lesson to review the content and address any questions.

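### Covariates for the primary model are chosen by significance tests of group differences, so the model is not fixed in advance and baseline headache days would rarely be adjusted for as a covariate

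*Protocol article*

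**What the plan says.** Section 2.10 sets out the primary model: "The model will include group and time as fixed effects, time by group as an interaction term, and the outcome as the dependent variable". It then gives the only rule for covariates: "Covariates will be selected from those identified as significantly different between groups [10"]. No covariate is named in advance.

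Other sections that bear on this:
- Section 2.3: "Patients will be randomly assigned at a 1:1 ratio", from a list generated beforehand.
- Section 2.4: "patients will complete a headache diary for one month before entering the study (T1"). Baseline headache days are therefore available for every randomised patient.
- Section 2.2: "The primary outcome will be the reduction in monthly headache days from baseline to follow-up".
- Abstract: "Treatment effectiveness was evaluated at baseline (T1) and 2 months after the end of treatment (T4").
- Section 2.10, sample size: "we aim for a between group difference of 3.0 monthly headache days at T4 and a standard deviation of 4.5".

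The article does not say whether T1 is one of the model's time levels. Section 2.2 and the abstract suggest that it is. It also does not say whether the SD of 4.5 describes T4 values or changes from baseline.

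**The concern.** Under valid randomisation a significant baseline difference is a chance event. Testing for it does not show whether a variable predicts the outcome, and prediction is the reason to adjust. The rule can admit an irrelevant variable that happens to be unbalanced and pass over a strongly prognostic one that happens to be balanced. The same measure taken at baseline, T1 headache days, is the obvious covariate to fix, yet it is subject to the same lottery.

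Two things are at stake. The primary model cannot be written down before the data are seen. And precision that could be had at no cost may be lost in a trial planned around 35 patients per arm. This is a method the protocol states, not a detail left to an analysis plan: a plan that follows the sentence inherits the problem.

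**Working it through.** **1. The plan's own figure.** Inputs from Section 2.10: difference 3.0, SD 4.5, alpha 5% (two-sided assumed), power 80%. Per arm, n = 2 × (4.5 × (1.960 + 0.842) / 3.0)² = 35.3, or 70.6 in total, against the stated 70 (72 if each arm is rounded up). The stated size thus matches a plain two-group comparison with no gain from baseline. The checks below use 35 per arm.

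**2. How often the rule adjusts for baseline headache days.** I read the rule as testing baseline variables at 5%; the article does not state the level. Under randomisation the flag rate is then 5% (4.9% to 5.1% in 40,000 simulated trials per setting). The covariate is left out in about 95% of trials. For k independent candidates the chance that at least one is flagged is 1 − 0.95^k: 23%, 34% and 40% for k = 5, 8 and 10. These are illustrations only, since the article gives no candidate list.

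**3. What the model does otherwise.** If T1 is a time level, the T1-to-T4 group-by-time contrast with complete data is the difference in mean change. Let ρ be the T1–T4 correlation and s the T1 SD, and treat the model as linear:
- SD of change = √(s² + 4.5² − 2 × ρ × s × 4.5)
- SD after baseline adjustment = 4.5 × √(1 − ρ²)

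Neither ρ nor s is in the article, so both are assumed. Power is by noncentral t, 35 per arm, difference 3.0:

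| ρ | Adjusted: SD, power | Change, s = 4.5: SD, power | Change, s = 3.0: SD, power |
|---|---|---|---|
| 0.3 | 4.29, 82% | 5.32, 64% | 4.60, 77% |
| 0.4 | 4.12, 85% | 4.93, 71% | 4.30, 82% |
| 0.5 | 3.90, 89% | 4.50, 79% | 3.97, 88% |
| 0.6 | 3.60, 93% | 4.02, 87% | 3.61, 93% |

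Comparing T4 alone gives 79%. With equal SDs the change contrast has 2/(1 + ρ) times the adjusted variance: 1.54 at ρ = 0.3 and 1.33 at ρ = 0.5. Below ρ = 0.5 it is then also worse than T4 alone.

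**4. If the SD of 4.5 is for change.** Change-score power is about 79% at every ρ. With equal SDs the adjusted SD is 4.5 × √((1 + ρ)/2), which is 3.63 at ρ = 0.3 and 4.02 at ρ = 0.6. Adjusted power is then 93% and 87%.

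**5. Type I error.** The rule was simulated under the null with baseline headache days as the only candidate and equal SDs. With T4 alone as the fallback analysis, the rejection rate is 4.7%, 4.3% and 3.6% at ρ = 0.3, 0.5 and 0.7. With the change score as the fallback, it is about 4.3% to 4.5% at ρ = 0.5 and 4.6% at ρ = 0.7. None exceeds 5%.

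**The case against.** The other side has four good arguments, and each limits the point.

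**Baseline is not ignored.** A reader might infer that the analysis usually leaves baseline out. If T1 is in the response, as Section 2.2 and the abstract suggest, the group-by-time term uses baseline in every trial. What is rarely done is adjustment for it as a covariate. That is a loss of efficiency, not an omission. This stands.

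**The loss may be small.** A reader might take 64% or 71% as the trial's real power. Those figures need a T1 SD equal to the T4 SD and a low correlation. Entry requires chronic migraine (described in the Introduction as more than 15 days a month), and a month caps the count, so T1 values are range-restricted while T4 values can fall freely. A smaller T1 SD is therefore plausible. At 3.0 the gap is 5 points at ρ = 0.3 and none to the nearest point at ρ = 0.6. If the SD of 4.5 is for change, power stays close to plan. This stands too: the documents cannot settle the size.

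**False positives are not shown.** A reader might infer that data-driven selection inflates type I error. The simulations show a slightly conservative rule.

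**The number of chance entries is unknown.** Assuming 10 to 15 independent candidates gives 40% to 54%, but the article supplies no such count. The disability, sensitisation and mood scales in Section 2.1 plausibly overlap, and the wording does not say that every flagged variable enters.

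None of this rescues the rule itself. Nothing else in the article overrides it, and the literature reference attached to it shows precedent, not validity.

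**Conclusion.** The concern holds as a defect in the stated method, and it should be fixed. The primary model is not fixed in advance, and its covariates would be picked by chance imbalance. Baseline headache days would enter as a covariate in about 1 trial in 20, assuming a 5% selection test.

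Against prespecified baseline adjustment, the change-score contrast gives up from 18 percentage points of power (ρ = 0.3, T1 SD 4.5) to almost none (ρ = 0.6, T1 SD 3.0). This rests on 35 per arm, a difference of 3.0, a T4 SD of 4.5, and T1 being a time level. Across the values examined, adjustment is never the less precise choice.

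Neither bias nor an inflated error rate is shown: simulated type I error is about 3.6% to 4.7%. The harm is lost precision and a data-dependent primary analysis, which supports a recommended correction rather than a fatal objection.

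**What to change.** Delete the significance-based selection in Section 2.10. State that T1 monthly headache days are in the primary model regardless of observed balance, in one of two ways: T1 as a covariate with T3 and T4 as responses, or T1 kept in the response with its mean constrained equal across arms. Either choice also settles whether T1 is a time level.

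Further covariates are optional. Medication overuse and preventive therapy are candidates, since Section 2.1 admits patients with or without either: "Patients on migraine preventive therapy will be included if their prophylaxis has remained unchanged and ineffective for at least three months prior to recruitment". The article does not show that they predict T4 headache days, so any that are added should be named now on prognostic grounds and kept whatever the balance.

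The cost is one sentence, and nothing new is collected. It should be done before outcome data are seen, because a covariate set chosen later cannot be presented as prespecified.

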TNE is defined as an “educational program aimed at improving the comprehension of pain mechanism, enhancing the coping strategies and increase the patients’ quality of life” [19]. In contrast, conventional anatomical and biomedical education not only showed limited or no efficacy in decreasing pain and disability in patients but might even increase fear, catastrophizing, and pain levels, inducing a nocebo effect [20]. TNE aims to increase knowledge of pain neurophysiology and neurobiology, pain representation, and the meaning of pain and to improve coping strategies [21,22,23]. It also shows effectiveness in reducing pain intensity and migraine disability and improving patients’ moods, with a positive clinical benefit in terms of pain rating, pain-related disability, catastrophizing, and physical performance [24,25] when applied to patients with chronic musculoskeletal pain.

Functional magnetic resonance studies showed that TNE exerts an effect by reducing the activity of several areas belonging to the cerebral pain network [21], suggesting that this intervention could be monitored by neural biomarkers.

Migraine prevention generally requires several months of treatment, either with pharmacological or non-pharmacological therapies. Therefore, a predictive marker could be of great interest, since an early change occurring before the effect of treatment could help in selecting patients or reducing the time of administration of the treatment itself if unnecessary.

Several available and easy-to-perform neurophysiology techniques can be used to highlight the benefit of systemic [26], local [27], and neuromodulatory [7] treatments for migraine. The intensity dependence of auditory-evoked potentials (IDAP), a non-invasive measurement of serotonergic firing from brainstem to cortex, predicted recovery from chronic to episodic migraine after the administration of a single greater occipital nerve block [27].

Also, the nociceptive blink reflex (nBR) was found to be sensitive to changes in excitability induced by transcranial magnetic stimulation and flashlight, biofeedback, and some medications [28,29,30].

Clinically, quantitative sensory testing (QST) was found to effectively assess somatosensory function and differentiate between various phases of the migraine cycle, as responses to different stimuli vary throughout these phases [31].

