### 2.8. Therapeutic Neuroscience Education

QST provides insight into the overall state of central nervous system (CNS) sensory amplification. It is typically conducted by applying peripheral stimuli (e.g., electrical, mechanical, thermal, or vibratory) and evaluating the CNS response. For this reason, QST is considered an indirect measure of sensory processing [50].

Studies have demonstrated that QST can predict chronic pain trajectories, assess the risk of pain chronification, and determine treatment outcomes [51].

Different QST modalities have been extensively investigated in migraine patients since the 1950s [34], yet significant heterogeneity remains in assessment methods. A recent systematic review with meta-analysis on QST in migraine patients concluded that alterations in somatosensory function in migraine are specific to the stimulus modality, measurement approach, and anatomical location [52].

The content of the program in the TNE-A group will align with established literature on the topic adapted from “Explain Pain” and “Explain Pain Supercharged” [53,54]. The TNE intervention will consist of ten one-hour group lectures delivered over a 10-week period. Groups will be composed of a moderate number of participants (4 to 8 individuals) to encourage interaction and participant feedback. The program will be administered by two dedicated experts, both of whom underwent standardized training by the same specialist to ensure consistency and reliability in the intervention, as supported by findings from an unpublished pilot feasibility study.

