The program in the CON-A group will also consist of ten learning sessions, but instead of focusing on the individual–pain interaction, it will cover the following topics: the classification of headaches according to the ICHD-3 criteria; an overview of migraine, including its definition, symptoms, epidemiology, and genetics; migraine pathophysiology, where we will explain both mechanisms leading to pain during an attack and those that contribute to the recurrence of migraine attacks over time; a biomedical model of pain (explaining the association between tissue damage/inflammation and pain perception); the definition of chronic migraine, the mechanisms of migraine chronification, and how migraines can revert to an episodic form; an explanation of the prodromal and postdromal phases of migraine as well as trigger factors; a discussion on the classes of medications used in migraine management and general information on treatment strategies; the role of passive interventions in pain management; and a look at migraine comorbidities as well as the anatomy and biomechanics of the cervical spine. The final session will be a summary of the key points discussed in the previous nine sessions.

In both groups, patients will be assigned homework between sessions, primarily consisting of cognitive exercises such as reflecting on the material covered or explaining the concepts they learned to someone else in simple terms. This approach will help patients mentally organize the new information, reinforcing their understanding and retention of these concepts.

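### Adverse events are tabulated by arm for the 10-week treatment period only, so the two months up to the T4 efficacy assessment (44% to 47% of T1 to T4) have no planned count

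*Protocol article*

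**What the plan says.** Section 2.10 (Plans for Analysis) states the safety tabulation: "The number of adverse events (AEs) during the treatment period will be counted separately for the TNE-A and CON-A groups". Events are graded by CTCAE and defined without regard to causality. Relationship to treatment, action taken and outcome are summarised separately. No other section gives a window for adverse events.

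The treatment period has a defined length. Section 2.8 describes "ten one-hour group lectures delivered over a 10-week period", and the Abstract places the end of treatment at T3, 10 weeks after the start.

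Efficacy is judged later. The Abstract says "Treatment effectiveness was evaluated at baseline (T1) and 2 months after the end of treatment (T4"), section 2.4 says "headache burden will be reassessed two months after completing the TNE program (T4"), and the sample size in section 2.10 targets a difference of 3.0 monthly headache days at T4.

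Two further passages bear on possible harm. The Introduction says that "conventional anatomical and biomedical education not only showed limited or no efficacy in decreasing pain and disability" and that it "might even increase fear, catastrophizing, and pain levels, inducing a nocebo effect". The control programme in section 2.8 includes "a biomedical model of pain (explaining the association between tissue damage/inflammation and pain perception") and also "the anatomy and biomechanics of the cervical spine".

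**The concern.** Benefit and harm are assessed over different windows. The efficacy comparison runs to T4 and the adverse event comparison stops at T3. The article itself gives a reason to look for harm in both arms for as long as efficacy is followed: it says that education of the type partly used in the control arm may raise fear, catastrophizing and pain.

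What is at stake is the completeness of the harms comparison, not the primary test. Events between T3 and T4, with their grade, relationship to treatment, action taken and outcome, would not appear in the planned tables. A reader weighing the T4 result would have no matching safety summary for the period just before it.

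**Working it through.** **Inputs**
- Treatment period: 10 weeks (Abstract; section 2.8). The Discussion gives one lesson per week, and 10 lessons × 1 week = 10 weeks, so the article's own timing of T3 reproduces.
- Follow-up after treatment: two months (Abstract; section 2.4). The article gives no figure in weeks, so I assume w = 8 to 9 weeks, with 8.7 weeks for two calendar months.
- Recruits: 80, allocated 1:1, so 40 per arm (sections 2.10 and 2.3).

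**Share of T1 to T4 without an adverse event count**

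Share = w / (10 + w)
- w = 8: 8 / 18 = 44.4%
- w = 8.7: 8.7 / 18.7 = 46.5%
- w = 9: 9 / 19 = 47.4%

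The stated window therefore covers 53% to 56% of the period.

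**Person-time per arm, assuming 40 patients and no dropout**
- Counted now: 40 × 10 = 400 person-weeks
- Counted to T4: 40 × 18 = 720 to 40 × 19 = 760 person-weeks
- Difference: 320 to 360 person-weeks per arm

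**What would be seen between T3 and T4 under the plan**

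| Kind of harm | Planned source after T3 | Visible by arm? |
|---|---|---|
| More headache days | Diary kept throughout the study (2.1); headache burden at T4 (2.4); model with group, time and interaction (2.10) | Yes, as an outcome |
| Greater pain intensity or acute medication use | Diary (2.1) | Recorded, but not as an adverse event |
| Fear, catastrophizing, anxiety, depression | PCS and HADS are among the questionnaires (2.1), which the Abstract and 2.4 place at T1 and T3 | No planned T4 measurement clearly stated |
| Any other adverse event | None stated | No |

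The gap thus lies in the last two rows. No sample size formula enters, and the 3.0-day difference, the standard deviation of 4.5, alpha and power are untouched by the choice of window.

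**The case against.** The strongest case against has five parts.

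1. A reader might infer that control patients could worsen after T3, that this would pass as TNE efficacy at T4, and that nothing would reveal it. The documents do not support this. The diary runs throughout, T4 headache burden is collected, and the model includes time and group by time. A rise from baseline in the control arm would show as such. Attributing a T4 difference to a poor comparator is a matter of comparator choice, and a longer safety window would not remove it. This part stands in full.

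2. The Introduction says nothing about onset after teaching ends. Effects of biomedical education may well arise during the ten sessions, when adverse events are counted, and would be picked up by the questionnaires at T3. That passage also concerns conventional education in general. The biomedical model is one control topic among many, and the Discussion says that content affecting the understanding of pain was deliberately left out. That last statement sits poorly with the topic list in section 2.8, but the rest stands: delayed harm is possible, not predicted.

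3. Section 2.1 measures migraine burden by diary and questionnaires together, so the T4 reassessment of headache burden might include PCS and HADS. The Abstract and section 2.4 point the other way. A complete gap at T4 is not proved, but even T4 questionnaires would not be an adverse event count.

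4. The article does not say that later events are excluded, and the full protocol may collect them. This stands in part. The restriction to a single window is my reading, but the article names that window and no other, so this is a stated choice and not a detail left out.

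5. An on-treatment window is ordinary for a low-risk educational intervention. That is fair, and it limits the weight of the point.

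**Conclusion.** The point holds as a low-severity, inexpensive improvement. The planned adverse event tabulation ends at T3, efficacy is judged at T4, and 44% to 47% of the T1 to T4 period has no planned count. The range depends only on how two months is converted to weeks.

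The percentage is a share of calendar time. A reader might take it as the share of harms missed, but the article gives no event rates or timing that would allow that reading. Nor is headache worsening among the things missed, since it is captured as an outcome. What is missing from the comparison is other adverse events and any late fear, catastrophizing or mood effects between T3 and T4.

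This rests on taking the treatment period to end at T3, as the Abstract defines it, and on the questionnaires being given at T1 and T3 only, as the Abstract and section 2.4 indicate.

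**What to change.** Amend section 2.10 so that adverse events are counted and tabulated by arm from randomisation to T4, with T1 to T3 and T3 to T4 shown separately. At the T4 assessment, ask each patient about events since T3, and apply the same CTCAE grading and the same summaries of causality, action taken and outcome.

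The existing definition already covers worsening of any kind, so it needs no change. It would help to state in section 2.4 whether the T4 reassessment includes PCS and HADS. If the sponsor prefers to stop counting at T3, the reason should be given.

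The cost is one added question and slightly more data entry. The Discussion lists hospital attendances at T1, midway and the final lesson only, and the article does not say how T4 data are obtained, so the question should go with whatever contact collects the T4 headache data. Sample size, alpha, power and the primary analysis stay as they are.
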